## Abstract

**Supplementary Information:**

The online version contains supplementary material available at 10.1007/s12028-023-01755-9.

## Introduction

Traumatic brain injury (TBI) is a global public health emergency. It is the leading cause of death in young adults, and it is a major cause of death and disability in all ages worldwide. The impact is felt by patients, families, and communities. In the United Kingdom, the annual cost is estimated at £15 billion, with more than 68,000 years of life lost [1, 2].

Neuroprotection is the preservation, salvage, or recovery of central nervous system function after acute insult. Better neuroprotective strategies would reduce death and disability after TBI. The current management strategies are conservative, relying on provision of physiological stability and timely management of complications (e.g., seizures, intracranial hypertension). There is no proven therapy that provides additional benefit [3].

There are plausible reasons to consider beta-blockers as potential neuroprotective drugs after TBI. Plasma catecholamine levels correlate with inflammation, endothelial injury, and poor outcome after TBI [4–6]. In animals, administering beta-blockers after TBI reduced cerebral edema and hypoxia (mice), increased perfusion (mice), and protected cerebral autoregulation (pigs) and it was associated with better recovery (mice) [7–9].

In patients a number of meta-analyses show that there is potential benefit for beta-blockade in TBI to reduce mortality and improve functional outcomes [10–14]. However, the studies are heterogenous and largely observational. A few small, randomized trials are supportive but have limited external validity and/or have not been subject to peer review [15–18]. This means there is still uncertainty about the overall effectiveness of beta-blockade as well as the specifics of patient selection, drug, dose, route, and physiological goal.

Repurposing an established beta-blocker for neuroprotection could significantly improve individuals’ health outcomes, reduce the impact on families and communities, and save resources for health systems and societies at a low cost, potentially representing excellent value for money. There is, however, a risk with the use of antihypertensive drugs early after severe TBI; compromising blood pressure maintenance in the group of patients with TBI, for whom hypotension has been called “the single most important secondary insult,” could lead to worse outcomes [19].

With this risk–benefit balance in mind, we designed the Early Beta-Blockade in adults after severe Traumatic Brain Injury (EBB-TBI) program, of which this is the first of three planned studies. The overarching hypothesis of the EBB-TBI program of research is that beta-1 adrenoceptor blockade after severe TBI in adults reduces morbidity and mortality by reducing secondary brain injury driven by the hyperadrenergic state. Here, we describe the protocol for the first study. We use methodology common to early phase drug studies to test escalating starting doses for esmolol infusion in small cohorts of patients with an end point of heart rate control without compromise of cerebral perfusion pressure (CPP). The aim is to optimize the intervention with esmolol so it can then be tested in subsequent trials of efficacy and effectiveness.

### Rationale for Choice of Esmolol and Dosing Regimen

There are several characteristics of esmolol that are well suited to use for beta-blockade in the early phase of critical illness. First and foremost, the rapid onset (time to steady state of action of 5 min), facilitates titration to the desired clinical end points. This, coupled with the short elimination half-life of 9 min, means rapid offset of effect if reduced or stopped for adverse events. The drug has few interactions with other medications beyond the general class effects of beta-1 selective-blockers. It is metabolized to inactive compounds, and this is independent of organ function. The intravenous route of administration bypasses the gut and guarantees drug delivery in a population where gastric emptying is frequently delayed. Finally, it is inexpensive, in common use in intensive care units (ICUs), and straightforward in its preparation and administration (e.g., it is stable at room temperature for up to 24 h, protection from light is not required, and it can be administered via peripheral venous access) [20, 21].

Although the primary reason for choosing esmolol is practical, there are also theoretical arguments. A beta-1 selective blocker (metoprolol) is used in the Lund approach to the management of TBI because it does not cause cerebral vasodilatation or alter cerebral blood flow after severe TBI [22, 23]. Esmolol itself has been shown to have no adverse effect on cerebral blood flow in volunteers or in patients receiving electroconvulsive therapy [24, 25]. In the setting of anesthesia, with the same drugs commonly used for sedation after TBI, esmolol provides additional cortical suppression that could contribute to neuroprotection [26]. In animals, esmolol is neuroprotective after brain or spinal cord ischemia [27, 28]. Finally, there is evidence that esmolol reduces the inflammatory response after surgical trauma [29].

The initial dosage selected for testing in the first cohorts in the EBB-TBI study (esmolol infusion started at 5 µg per kilogram per minute [mcg.kg.min^-1^]) is based on a regimen shown to be tolerated by a population with severe septic shock who are, like many patients after severe TBI, mechanically ventilated and receiving vasopressors [30]. The esmolol was then titrated against heart rate using dosage increments of 2.5 mcg.kg.min^-1^ every 30 min. The infusion starting rate for subsequent cohorts was determined by using the so-called modified Fibonacci sequence (commonly used in oncology dose-finding studies [31, 32]) using the initial EBB-TBI cohort dosage as the start of the sequence.

Dosages as low as 15 mcg.kg.min^−1^ are anti-inflammatory after surgical trauma in humans [29]. The effective concentration (EC50) for reduction in heart rate during exercise in humans is 113 mcg.kg.min^−1^ [33]. Side effects, mainly hypotension, are more common with dosages exceeding 150 min^−1^ [20, 33]. In rats a dosage of 20 mcg.kg.min^−1^ is protective against cerebral ischemia, and 16 mcg.kg.min^−1^ is anti-inflammatory in sepsis [34, 35]. Although the minimum dosage required for neuroprotection in humans is not known, this supports the concept that a dosage of esmolol resulting in heart rate reduction is also potentially effective in reducing brain injury and that neuroprotection might be possible while avoiding serious side effects.

Rather than a fixed dosage, the infusion will be titrated to heart rate, a convenient clinical biomarker for sympathetic nervous system activity and catecholamine drive, allowing for personalization of dosage. We will aim for a 15% reduction from preenrollment baseline. Titration of medication to achieve physiological goals is routine in intensive care practice. Use of heart rate avoids any conflict with accepted physiological goals like blood pressure set in clinical guidelines (such as those from the Brain Trauma Foundation [19]).

In healthy volunteers, heart rate reduction of 15% induced by esmolol did not alter cerebral blood flow [24]. After ST elevation myocardial infarction (STEMI), a 14% reduction in heart rate with esmolol did not increase the incidence of cardiogenic shock or atrioventricular block while limiting the peak cardiac troponin T release [36]. A 20% reduction in heart rate in septic mechanically ventilated patients did not alter oxygen utilization or hepatic or leg blood flow [37]. Evidence relating to the ideal target heart rate in severe TBI is conflicting [38, 39].

We aim to administer esmolol as soon as practicable after injury to achieve early blockade of the hyperadrenergic surge accompanying the head trauma and interruption of self-perpetuating pathophysiological cascades before secondary injury is established [40]. Observational data show catecholamine related pathophysiology at the time of hospital admission for TBI [5]. The duration of the infusion is limited to 4 days from enrollment. This translates into an intervention period that spans the time of initial development of cerebral edema after injury. This regimen is therefore based on a combination of clinical judgment of the time of greatest sympathetic activation with knowledge of the typical course of intracranial hypertension [41, 42]. It allows the primary research question for this study to be answered at the time of greatest potential hemodynamic instability without unnecessarily prolonged exposure to a drug that may not ultimately provide benefit. After this period, the continued use of esmolol or any other selective or nonselective beta-blocker is at the discretion of the treating clinician. To the best of our knowledge, there is no literature examining the optimal timing of administration of beta-blockers after traumatic, ischemic, or septic insult.

### Rationale for Use of Continual Reassessment Method

Dose-finding studies are used in early-phase research to estimate the dose-toxicity profile of drugs and to select the right dose for subsequent trials. Rule-based study designs rely on predefined rules to determine future dosage decisions based on observed toxicity at current doses. In contrast, model-based designs use statistical models to guide these decisions based on a target level of toxicity that combines judgments of the potential benefit of drug administration and severity of harm arising from toxicity.

The continual reassessment method (CRM) is a parametric model-based study design. Several advantages are reported for model-based designs like the CRM over traditional rule-based designs, including flexibility and increased precision. This aids an efficient study design that will minimize the number of patients required to determine the maximum tolerated dose and maximizes safety by exposing the fewest patients possible to either undertreatment or overtreatment and by rapid dose titration [43–46].

Additional safety measures are possible with the CRM without compromising the study performance [47]. Given the lack of data on early esmolol dosing in TBI, the uncertain magnitude of any benefit, and the potential for severe harm with toxicity (i.e., hypotension), this is important for this study. A run-in cohort of three patients, increased number of cohorts, and avoidance of skipping untried doses have been incorporated in this protocol.

### Study Outline

This is a prospective dose-finding study of esmolol aiming to attenuate the sympathetic surge associated with severe TBI in adults. The setting is the 48-bed mixed ICU of Southmead Hospital, Bristol, a 996-bed teaching hospital in the southwest of England, and a major trauma center serving an adult population of approximately 2.3 million. On average, the ICU admits more than 130 patients with severe TBI annually.

The primary objective is to define a treatment dosage escalation schedule for esmolol for use in adults early (< 24 h) after severe TBI that balances the potential benefit of early exposure to beta-blockade with the ability to maintain adequate CPP. A reduction of heart rate of at least 15% from preinfusion baseline will be used as an indicator of clinically significant beta-blockade.

A group sequential adaptive model-based design (the CRM) will be used to determine the maximum tolerated dosage schedule for esmolol, defined as the highest dosing regimen associated with an acceptable level of toxicity. For the purpose of this study, this is taken to be a probability of dose-limiting toxicity of 10%. Dose-limiting toxicity is defined as failure to maintain CPP above the minimum recommended by Brain Trauma Foundation guidelines (60 mm Hg), despite standard interventions including vasopressors and the protocolized deescalation of the esmolol infusion such that withdrawal of esmolol is required, or the occurrence of a serious adverse event mandating withdrawal of the esmolol infusion.

Secondary objectives are to identify the effects of esmolol on organ function and to record clinical outcomes including mortality and function at 6 months. Exploratory objectives are to monitor the effects on biomarkers of sympathetic nervous system activity and to gather data to inform the design of a randomized controlled trial to establish feasibility and efficacy.

### Study Flow Chart

Flow through the study is shown in Fig. 1.

**Fig. 1 Fig1:**
[figure not shown]
Flow of patients through the study. ICU, intensive care unit

### Eligibility

Participants must meet all inclusion criteria and none of the exclusion criteria (shown in Table 1) and start the esmolol infusion within 2 h of confirmation of eligibility. The baseline heart rate must be > 60 beats per minute for more than 15 min for the infusion to start.

**Table 1 Tab1:** Eligibility criteria

Inclusion criteria (all to be met)	Exclusion criteria (none to be met)
1. Aged 18 years or more	1. Life or limb threatening extracranial injury (in the opinion of the treating intensivist)
2. Severe traumatic brain injury (Glasgow Coma Score of 8 or less after resuscitation or prior to intubation)	2. Perceived devastating brain injury admitted for the purposes of prognostication or organ donation
3. Within 24 h of injury	3. Participation in another clinical trial of investigational medicinal product within preceding 30 days
4. Intracranial pressure monitoring in situ	4. Pregnancy
	5. Breast feeding
	6. Hypersensitivity to beta-blockers
	7. Cardiogenic shock
	8. Decompensated heart failure (NYHA class 4)
	9. Untreated sick sinus syndrome or AV nodal conduction disorders including second-degree or third-degree heart block)
	10. Untreated phaeochromocytoma
	11. Acute severe bronchospasm
	12. Severe pulmonary hypertension (mean PA pressure > 55 mm Hg)
	13. Prinzmetal’s angina
	14. Severe metabolic acidosis (pH < 7.1)
	15. Use of verapamil within the preceding 48 h

AV, atrioventricular, PA, pulmonary artery, NYHA, New York Heart Association

These criteria exclude those at greatest risk of harm from beta-blockade, target early enrollment for greatest potential benefit and remain broad to capture a representative patient population.

### Consent

Potentially eligible participants, because of their severe TBI, will lack the capacity to provide consent for this study. The need for early intervention to maximize potential benefit, and the uncertainty of time and extent of recovery, means it is not practicable to wait for capacity to return. The time critical nature of the intervention and the potential for significant additional distress in the emergency situation precludes seeking prior personal legal representative opinion. As such, an emergency waiver of consent model will be used, with informed consent sought once patients regain capacity, as laid out in UK legislation (The Medicines for Human Use [Clinical Trials] Amendment [No.2] Regulations 2006).

Although any participant (or their legal representative) may withdraw their consent at any time, given the adaptive nature of the study with frequent analysis of patient data and the dependence of later study drug dosing on prior patient response, it is not feasible to withdraw all data unreservedly. Participant data that has been used in study drug dose calculation will not be withdrawn.

### Study Intervention

Open-label esmolol is given as a continuous intravenous infusion at a dosage of 2.5–200 mcg.kg.min^−1^ titrated using a predefined dosage escalation schedule to achieve a heart rate reduction of ≥ 15% from baseline with CPP maintained above 60 mm Hg. The target heart rate will be set as the rolling mean over the preceding 5 min to avoid overshoots. Baseline is defined as the mean heart rate in the 4 h preceding confirmation of eligibility. The minimum permitted target heart rate will be 60 beats per minute, even if this is less than 15% reduction from baseline; the maximum will be 100 beats per minute, even if this is more than a 15% reduction from baseline. Actual body weight at the time of enrollment in the study (estimated or known) will be used for dosage calculations.

A starting dosage is defined for each cohort, with dosage increments for that cohort being 50% of the starting dosage. The dosage is reviewed and adjusted every 30 min as required to achieve the target heart rate (± 5 beats per minute). Titration to achieve heart rate control for short lived stimulating procedures (e.g., tracheal suction, positioning, portable chest X-ray) is not required. The infusion should be continued during procedures including surgery or within hospital transfers for imaging.

When the infusion is restarted after temporary suspension (e.g., for bradycardia or if heart rate maintained in target range without need for infusion), the starting dosage for that level will be used with increments every 30 min as required. The infusion should not be restarted after a temporary suspension until the heart rate exceeds the minimum target rate (or 60 beats per minute) for more than 15 min.

Esmolol infusion continues according to study protocol until one of the following stopping rules is met:Ninety-six hours from start of infusionHeart rate target achieved without esmolol for > 12 hDose-limiting toxicityDeath or withdrawal of life-sustaining treatmentRequest of participant, legal representative, or treating clinicianICU discharge or transfer to nonparticipating ICU

The esmolol is weaned in steps of 5–10 mcg.kg.min^−1^ every hour from 96 h to avoid rebound tachycardia. In the event of dose-limiting toxicity, it may be reduced more quickly or stopped immediately. In the event of ICU discharge or transfer to a nonparticipating ICU, the infusion will be reduced at a rate calculated to ensure at least 2 h without esmolol infusion prior to discharge.

Bradycardia is defined for the purposes of this study as a heart rate under 50 beats per minute. The dosage of esmolol should be reduced in the appropriate increments for dosage level every 30 min until the bradycardia resolves.

Bradycardia with hemodynamic compromise is a heart rate under 50 beats per minute and a systolic blood pressure under 110 mm Hg (or 100 mm Hg for those aged 50–69 years). The dosage of esmolol should be reduced by twice the appropriate increment for dosage level every 30 min until bradycardia with hemodynamic compromise resolves.

When bradycardia is severe (defined as heart rate under 30 beats per minute), the esmolol infusion may be stopped temporarily until bradycardia resolves. Further intervention is at the discretion of the clinical team including intravenous antimuscarinic or chronotropic drugs and external or transvenous pacing.

Second-degree heart block without bradycardia or hemodynamic compromise should be managed by weaning esmolol as at the end of the intervention period. If hemodynamic compromise occurs, or in the event of third-degree heart block, management is the same as for severe bradycardia.

Hypotension should be managed according to usual clinical practice, taking into account cardiac status and CPP target. Fluid resuscitation and use of vasoactive agents including catecholamine and noncatecholamine vasopressors and inodilators are permitted. Esmolol infusion should be reduced in increments if these measures are insufficient to maintain CPP.

Flow charts for the management of esmolol infusion are shown in Figs. 2 and 3.

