### Primary Outcome

The primary end point is a continual reassessment method-derived maximum tolerated dosage escalation schedule for esmolol that combines clinically significant reduction in heart rate (defined as ≥ 15% from baseline) with maintenance of CPP.

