### Statistical Analysis

Inability to maintain CPP in the presence of esmolol was chosen as the primary definition of toxicity based on the known importance of adequate blood pressure for prevention of secondary brain injury [19]. The maintenance of adequate CPP as a key goal of therapy is also familiar to clinicians practicing in the field of neurointensive care.

Only data from esmolol-treated patients will be used in statistical analysis. Esmolol-treated patients are those who meet all inclusion criteria and no exclusion criteria, receive any dosage of esmolol within 2 h of confirmation of eligibility and 24 h of injury, and do not withdraw consent for use of data prior to use of that data in CRM analysis.

A one-parameter logistic model, initialized with skeleton parameters as per Table 2, will be used for the CRM modeling, with estimated probabilities revised as data emerge. This likelihood modeling algorithm will identify a maximum tolerated dose escalation schedule, with a defined prior reasoned target toxicity level, or “acceptable” toxicity rate (*θ*), of 10% with an indifference level of 2 percentage points for decision making. The weighting afforded to the pretrial logistic model on estimated probabilities will be revised as trial data sequentially emerge.

**Table 2 Tab2:** Predefined dose levels for esmolol infusion

Dose level	Starting dosage (mcg.kg.min^−1^)	Increment (mcg.kg.min^−1^)	Estimated prior probability of dose-limiting toxicity
1	5	2.5	0.01
2	10	5	0.04
3	16	8	0.07
4	25	12.5	0.10
5	35	17.5	0.15
6	46	23	0.20
7	62	31	0.25

Cohort size of three will be used. In the absence of dose-limiting toxicity, an increase in the dosage escalation schedule will be considered by the trial management group after the last patient in a cohort has completed the esmolol intervention period. Dosage escalation cannot be by more than one level and, as an additional safety measure, the dosage will not be escalated until the second cohort has completed intervention. Dosage deescalation will be considered after each dose-limiting toxicity and is unrestricted. Dosage level changes are subject to sponsor approval with oversight of dosage decision making the responsibility of the Steering Committee comprising independent expert and lay members. The Steering Committee is also responsible for monitoring study conduct and safety in lieu of formal Data Monitoring and Ethics Committee given the setting and design of the study.

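### The primary end point claims a heart-rate reduction of at least 15%, but the schedule is selected on toxicity alone; one sentence also misdefines the target heart rate

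*Protocol article*

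**What the plan says.** **The end point.** Primary Outcome reads: "The primary end point is a continual reassessment method-derived maximum tolerated dosage escalation schedule for esmolol that combines clinically significant reduction in heart rate". It sets the reduction at 15% or more from baseline and joins it to maintained CPP.

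**The selection rule.** Study Outline says the maximum tolerated schedule is "defined as the highest dosing regimen associated with an acceptable level of toxicity", with acceptable toxicity set at a 10% probability of dose-limiting toxicity. A toxicity is CPP that cannot be held above 60 mm Hg despite standard measures and stepwise reduction, so that esmolol has to be withdrawn, or a serious adverse event that forces withdrawal. Statistical Analysis adds: "In the absence of dose-limiting toxicity, an increase in the dosage escalation schedule will be considered by the trial management group".

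**The role of 15%.** Study Outline states: "A reduction of heart rate of at least 15% from preinfusion baseline will be used as an indicator of clinically significant beta-blockade".

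**The titration rule.** Study Intervention takes the mean heart rate over the 4 hours before eligibility as baseline and aims for a 15% fall. The target may not go below 60 bpm, "even if this is less than 15% reduction from baseline", nor above 100 bpm. "The dosage is reviewed and adjusted every 30 min as required to achieve the target heart rate", within 5 bpm either way. The same paragraph says: "The target heart rate will be set as the rolling mean over the preceding 5 min to avoid overshoots".

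**Who may start.** Eligibility states: "The baseline heart rate must be > 60 beats per minute for more than 15 min for the infusion to start".

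**The concern.** The end point gives the selected schedule two properties. The selection rule tests one of them, tolerability. A schedule could be chosen because it produced few toxicities, be delivered exactly as written, and then be reported as combining a 15% reduction with maintained CPP, whatever the heart-rate response was.

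This matters because the Introduction says the optimized regimen is to go forward to efficacy and effectiveness trials. Those designing them would take the stated end point as evidence that the schedule produces clinically significant beta-blockade.

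The sentence on the rolling mean is a separate matter. A target equal to the current heart rate gives nothing to titrate towards, and the article is a public description of a regimen that others may want to use.

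**Working it through.** **1. Does heart rate enter the selection?** Set each element against the end point:

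| Element | Section | Heart-rate component? |
|---|---|---|
| Definition of dose-limiting toxicity | Study Outline | No |
| Model: one-parameter logistic, prior toxicity 0.01 to 0.25 | Statistical Analysis, Table 2 | No |
| Target: 10% toxicity | Study Outline, Statistical Analysis | No |
| Trigger to consider escalation: no toxicity | Statistical Analysis | No |
| Titration goal within every schedule | Study Intervention | Yes |
| Heart rate as a biomarker | Exploratory Outcomes | Yes, exploratory |

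The model's data are toxicities and patients per level. With the same toxicities, 0 of 24 and 24 of 24 patients reaching 15% lead to the same recommended level.

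Study Intervention also has esmolol reduced in steps when other measures do not hold CPP. That is a toxicity only if withdrawal is required. A patient turned down to a low rate who never reaches 15% therefore counts as having tolerated the schedule.

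**2. Does being on target imply 15%?** Let B be the 4-hour baseline. The target is T = min(max(0.85 × B, 60), 100), and the accepted band is T − 5 to T + 5. The reduction at rate h is 1 − h/B.

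- The floor applies when 0.85 × B < 60, so B < 60/0.85 = 70.6 bpm. The reduction at target is then 1 − 60/B: 3.2% at 62, 7.7% at 65, 11.8% at 68 and 14.3% at 70.
- The cap applies when 0.85 × B > 100, so B > 100/0.85 = 117.6 bpm. The target then gives more than 15%.
- The upper edge of the band reaches 15% only when 105/B ≤ 0.85, so B ≥ 105/0.85 = 123.5 bpm.

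| Baseline (bpm) | Target (bpm) | Reduction at target | Upper edge | Lower edge |
|---|---|---|---|---|
| 65 | 60 | 7.7% | 0.0% | 15.4% |
| 70 | 60 | 14.3% | 7.1% | 21.4% |
| 80 | 68 | 15.0% | 8.8% | 21.3% |
| 90 | 76.5 | 15.0% | 9.4% | 20.6% |
| 100 | 85 | 15.0% | 10.0% | 20.0% |
| 110 | 93.5 | 15.0% | 10.5% | 19.5% |
| 120 | 100 | 16.7% | 12.5% | 20.8% |

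The edges are limits, not expected values. The band is symmetric, so from 70.6 to 117.6 bpm its lower half exceeds 15%. The table shows only that a rate within the band and a 15% reduction are different quantities.

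**3. The target sentence.** If the target is the mean of the last 5 minutes, the difference between observed rate and target is about zero at every review. The same paragraph derives the target from a 4-hour baseline, with limits expressed against 15%. The two cannot both hold. The reference to avoiding overshoots suggests that the rolling mean is the smoothed observed rate.

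**4. How precise would an attainment figure be?** If all n patients at a level reach 15%, the exact 95% lower limit is 0.025^(1/n). For one cohort, n = 3, it is 0.29 (interval 29% to 100%). For two cohorts, n = 6, it is 0.54 (54% to 100%).

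**The case against.** The best defence is that what is selected is a schedule, meaning a starting dose with increments titrated to heart rate. Every candidate carries the 15% goal, and the CRM ranks candidates on tolerability. On that reading the end point describes the package. The rationale section calls 15% an aim and Study Outline calls it an indicator; neither promises it for each patient. This stands in part: heart rate is present in the intervention. But a goal shared by all candidates is not a property shown for the one chosen, and the end point is worded as such a property.

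A reader might infer that the 60 bpm floor and the 5 bpm tolerance are errors. The article does not support that. Both are openly declared; the floor is a sensible safety limit and the band an ordinary bedside tolerance. Nor can one infer that most on-target patients would fall short of 15%: the figures are edge values, and no baseline heart rates are given.

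A reader might also infer that attainment will go unreported. The article does not say so. Heart rate is an exploratory outcome, continuous exploratory variables are to be summarized, and the full protocol and analysis plan are not shown. The choice of on-infusion summary belongs there. The point concerns what the stated end point claims against the stated rules, not a missing table.

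On the rolling mean, the surrounding text makes the intention clear and the titration flow chart (Fig. 2) is not shown; it may be worded correctly. The sentence in the text is still wrong as it stands.

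**Conclusion.** The point holds as a minor one. The design delivers a toxicity-based maximum tolerated schedule. It does not test whether that schedule gives a 15% reduction, so the end point's wording goes beyond what the selection supports. The target sentence is a separate wording error.

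The effect is confined to the wording of the conclusion and of that sentence. A stronger reading, that dose allocation, toxicity estimates or patient safety are compromised, is not supported: the CRM does what Study Outline and Statistical Analysis say it does. The share of patients on target but short of 15% cannot be computed from the article.

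The arithmetic assumes that the intended target is 0.85 times the 4-hour baseline, limited to 60 to 100 bpm. That follows from the paragraph apart from the misworded sentence.

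**What to change.** 1. Describe the CRM output as the toxicity-based maximum tolerated schedule.
2. Report by dose level, as x of n and labelled descriptive, how many patients reached at least 15% below the 4-hour baseline. Note how many fell under the 60 bpm floor. Make any statement that the selected schedule combines the two properties depend on the 15% count.
3. Reword the target sentence: the target is 0.85 times baseline, limited to 60 to 100 bpm, and the rolling 5-minute mean is the observed rate compared with it.
4. Keep the floor, the cap and the tolerance band.

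Treatment, eligibility and the CRM do not change. Heart rate is already collected, so the cost is a few descriptive rows and some rewording. Enrolment began in December 2020, so the rows should be marked as added. The downside is that the 15% figure may look less favourable than attainment of the target band, and with three patients per cohort it will be imprecise.
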